### 3. STUDY DESIGN

#### 3.1. Study Overview

This study is a randomized, investigator-blind, subject-blind, sponsor-open, placebo substitution, sequential cohort, single dose escalation study of PNU-100480. In Cohort 1, each subject will receive 2 escalating single oral doses of PNU-100480 or placebo (Periods 3 periods, fasted). In Cohort 2, each subject will receive 2 escalating single oral doses of PNU-100480 or placebo (3 periods, fasted) and an open label dose of PNU-100480 under fed conditions (Period 4).

Subjects will undergo screening procedures within 28 days prior to dosing. Eligible subjects who meet the entry criteria will be admitted to the Clinical Research Unit (CRU) on Day 0 of each period and confined for at least 48 hours after dosing with either PNU-100480 or placebo.

Approximately 18 healthy volunteers, 18 to 55 years of age, males and females (women of non-childbearing potential only) will be enrolled in 2 cohorts with 9 subjects for each cohort and assigned to randomized treatment sequences within each cohort.

In each period, each subject will receive a single oral dose of either placebo or PNU-100480 under fasted conditions. Subjects in Cohort 2 will also receive an open label, single oral dose of PNU-100480 under fed conditions. For this period only, subjects will complete a high fat meal prior to dosing.

Planned doses may be adjusted up or down (within the planned limits) based on emerging safety and pharmacokinetic results from the previous dose period. Dose escalation will only proceed if safety of the previous cohort is deemed satisfactory, and none of the stopping criteria have been met.

#### Cohort 1:

| Sequences | Number of Subjects | Period 1 | Period 2 | Period 3 |
|-----------|--------------------|----------|----------|----------|
| 1         | 3                  | Placebo  | 100 mg   | 300 mg   |
| 2         | 3                  | 35 mg    | Placebo  | 300 mg   |
| 3         | 3                  | 35 mg    | 100 mg   | Placebo  |

#### Cohort 2:

| Sequences | Number of Subjects | Period 1 | Period 2 | Period 3 | Period 4 |
|-----------|--------------------|----------|----------|----------|----------|
| 1         | 3                  | Placebo  | 1000 mg  | 1500     | 600      |
| 2         | 3                  | 600 mg   | Placebo  | 1500     | 600      |
| 3         | 3                  | 600 mg   | 1000 mg  | Placebo  | 600      |

There will be an interval of at least 7 days between periods to allow for assessment of the preliminary safety, tolerability and PK data from the previous period.

Whole blood samples will be collected for the planned measurement of bactericidal activity in Cohort 1, Period 3, and Cohort 2, Periods 1, 2, and 3.

Excluding the screening period for up to 28 days, the study duration for each subject will be up to approximately 35 day for Cohort 1 and up to approximately 50 days for Cohort 2.

### 3.2. Human Pharmacokinetic Projections

Rat was selected for the prediction of human PK parameters for two reasons: 1) the in vitro metabolic rates (disappearance of the PNU-100480) using human liver microsomes were found to be qualitatively similar to rat liver microsomes 2) as per recommendation in the white paper for "Human PK Predictions" rat is the recommended species for human PK prediction when there is no knowledge which species is more predictive for human. Human clearance, volume of distribution at steady state, and elimination half-life for PNU-100480 from rats were projected as 53 mL/min/kg, 25.3 L/kg and 5.5 hour, respectively. Human oral bioavailability is predicted to be approximately 100%, this is projected from the bioavailability observed in rat which is >100%. Based on these predicted human pharmacokinetic parameters and the PK/PD relationship, a dosing regimen of 410 mg to 490 mg QD is predicted to be efficacious.

### 3.3. Dose Rationale and Stopping Rules

The planned potential PNU-100480 dose range to be evaluated in this study is 35 mg to 1500 mg. These doses were selected for: 1) characterization of PK and the safety of PNU-100480 over a wide range of doses; and 2) allow for exploration of doses that would achieve the projected combined efficacious exposure of 12 - 29  $\mu\text{g}\cdot\text{hr}/\text{mL}$  (Table 4). The projected exposure of PNU-100480 (parent) at doses 35 – 1500 mg are shown in Table 5 below. The expected pharmacokinetic exposure of PNU-100480 (parent) and two active metabolites (PNU-101603 and 101244) at planned doses of 35 mg to 1500 mg and safety margins are shown in Table 6 below.

The in vitro metabolic rates of formation of two metabolites and rate of disappearance of parent drug in human appears to be qualitatively similar to mouse and rat. Therefore, the relative ratios of two metabolites and parent drug were assumed to be same in mouse as well as in human. The relative ratios of two metabolites, PNU-101603 and PNU-101244 compared to PNU-100480 observed on day 24 in mouse (murine lung infection model) are 11 and 1.1, respectively. The two metabolites (PNU-101603 and PNU-101244) and PNU-100480 have similar in vitro antibacterial potency and therefore, a combined exposure of the three analytes will be used.

The exposures are calculated assuming linear pharmacokinetics of PNU-100480 as was observed in rat and dog over a wide range of doses and adding the exposure of two active metabolites using the relative ratios as defined above. The starting dose of 35 mg is approximately  $1/10^{\text{th}}$  of the HED of 338.7 mg calculated using 30 mg/kg NOAEL dose in the rat. The exposure at the starting single dose of 35 mg is also approximately  $1/14^{\text{th}}$  of the exposure at projected daily dose of 410 mg to 490 mg at steady state, which is expected to yield a combined AUC and  $C_{\text{max}}$  of 29  $\mu\text{g}\cdot\text{hr}/\text{mL}$  and 2.8  $\mu\text{g}/\text{mL}$ , respectively (Table 4). The

projected efficacious AUC of 12 - 29 µg·hr/mL is projected from the murine *M. tuberculosis* lung infection model and is associated with a significant effect.

**Table 5. Projected Exposures of PNU-100480 (Parent Only) after Administration of Single Dose to Humans**

| Dose (mg) | C max (µg/mL) a | AUC total (µg·h/mL) b |
|-----------|---------------------------------------|----------------------------------|
| 35        | 0.014                                 | 0.157                            |
| 100       | 0.04                                  | 0.449                            |
| 300       | 0.12                                  | 1.35                             |
| 600       | 0.24                                  | 2.69                             |
| 1000      | 0.40                                  | 4.49                             |
| 1500      | 0.60                                  | 6.74                             |

aCmax was calculated using the expression  $C_{max} = (F \cdot \text{Dose} / V) \cdot e^{-K \cdot T_{max}}$ ,  $T_{max} = \ln(K_a / K) / (K_a - K) = 2.75$  Hr

bCalculated using the relationship  $AUC = \text{Dose} \cdot F / CL$ .

CL = 222,600 mL/hr for a 70 kg human, F = 1, V = 1771 L for a 70 kg human, Ka was assumed as 0.8 hr

**Table 6. Projected Exposures and Safety Margin of Parent (PNU-100480) and Two Metabolites (PNU-101603 and PNU-101244) Relative to Rat 100 mg/kg Dose Exposures after Administration of Single Dose of Humans**

| Dose (mg) | Combined C max (µg/mL) a | Safety Margin Using Total C max b | Combined AUC Total (µg·h/mL) c | Safety Margin Using Total AUC d |
|-----------|------------------------------------------------|---------------------------------------------------------|-------------------------------------------|--------------------------------------------|
| 35        | 0.18                                           | 81.94                                                   | 2.06                                      | 59.23                                      |
| 100       | 0.52                                           | 28.68                                                   | 5.88                                      | 20.73                                      |
| 300       | 1.57                                           | 9.56                                                    | 17.65                                     | 6.91                                       |
| 600       | 3.14                                           | 4.78                                                    | 35.31                                     | 3.45                                       |
| 1000      | 5.24                                           | 2.87                                                    | 58.85                                     | 2.07                                       |
| 1500      | 7.86                                           | 1.91                                                    | 88.27                                     | 1.38                                       |

a Combined Cmax was calculated using relative ratio of PNU-101603 and PNU-101244 to PNU-101480 (parent) as 11 and 1.1, respectively.  
b Escalation limit for Cmax is 15 µg/mL based on the mean combined concentrations of two metabolites and parent at 100 mg/kg dose in rat (combined sexes).  
c Combined AUC was calculated using relative ratio of PNU-101603 and PNU-101244 to PNU-101480 (parent) as 11 and 1.1, respectively.  
d Escalation limit for AUC is 122 µg·h/mL based on the mean combined AUC of two metabolites and parent at 100 mg/kg dose in rat (combined sexes).

Since all 3 analytes are active and have similar pharmacologic activity, the proposed PK stopping criteria are based on the combined exposure of 3 analytes. The mean combined AUC and Cmax of the 3 analytes observed in rats (combined sexes) at 100 mg/kg are

122 µg·h/mL and 15 µg/mL, and will be used as the stopping criteria. If either of the exposure limits is reached, we will not proceed above that dose. Depending upon the total observed exposure, doses may be adjusted up or down to meet the exposure, but the maximum dose would not go above the exposure limit set for this study (AUC and Cmax of 122 µg·h/mL and 15 µg/mL, respectively).

The predicted exposure in humans at maximum dose of 1500 mg is approximately 1.5 fold less than rat exposure at the 100 mg/kg dose. Exposure at 100 mg/kg was used to set the stopping criteria as well as the safety margins because the adverse events observed at this dose were due to long term exposure to the drug, are monitorable in the clinic, and are not serious in nature. Stopping criteria based on combined exposure of all 3 analytes will be utilized to guide dose escalation. The main potential toxicity of PNU-101480 and its metabolites is related to inhibition of mitochondrial protein synthesis (MPS), an effect similar to Linezolid. The toxicity is delayed, readily monitored in clinic and reverses on drug discontinuation. As the MPS IC50 values of PNU-100480 and its metabolites are similar, it suggests that the toxicities of the parent and its metabolites due to MPS inhibition would be similar and additive. Therefore, combined exposure of PNU-100480 and its metabolites are proposed as stopping criteria.

Dose escalation will be contingent on the absence of all of the following:

1. Any serious adverse event in a subject receiving active drug.
2. Severe adverse events in the same organ system in ≥2 subjects receiving active drug in the same period.
3. Clinically significant ECG or BP/HR abnormalities in ≥2 subjects receiving active drug in the same period.
4. Clinically significant laboratory abnormalities in ≥2 subjects receiving active drug in the same period.
5. Other findings that, at the discretion of the investigator, indicate dose escalation should be halted.

The decision to proceed to the next higher dose will be made jointly by the sponsor and the investigator after careful review of available safety and tolerability, and pharmacokinetic information from previous cohorts and dosing periods. There will be an interval of at least 7 days between periods in Cohort 1 and 2 to allow assessment of the preliminary available safety and tolerability data.

The collection times for vital sign measurements, electrocardiograms (ECGs), safety labs, pharmacokinetic samples and the washout period may also be modified based on emerging safety and/or pharmacokinetic data. Duration of telemetry monitoring may be increased as appropriate if a clinically significant (as determined by the investigator) change in heart rate or other abnormal cardiovascular findings occurs within the first 12 hours after dosing.

Physical examinations, ECGs, vital sign measurements, and clinical laboratory tests will be performed and adverse events will be monitored throughout the study to assess safety and tolerability.

#### **4. SUBJECT SELECTION**

Approximately 18 healthy normal subjects, 18 to 55 years of age, males and females (women of non-childbearing potential only) will be enrolled into 2 cohorts, with 9 subjects for each cohort.

This study can fulfill its objectives only if appropriate subjects are enrolled. The following eligibility criteria are designed to select subjects for whom protocol treatment is considered appropriate. All relevant medical and non-medical conditions should be taken into consideration when deciding whether this protocol is suitable for a particular subject.

##### **4.1. Inclusion Criteria**

Subjects must meet all of the following inclusion criteria to be eligible for enrollment into the study:

1. Healthy male and/or female (women of non-childbearing potential only) subjects between the ages of 18 and 55 years, inclusive (Healthy is defined as no clinically relevant abnormalities identified by a detailed medical history, full physical examination, including blood pressure and pulse rate measurement, 12-lead ECG and clinical laboratory tests).
2. Body Mass Index (BMI) of 18 to 30 kg/m^2; and a total body weight >50 kg (110 lbs). A BMI lower limit of 17.5 kg/m^2 may be rounded up to 18.0 kg/m^2; a BMI upper limit of 30.5 kg/m^2 may be rounded down to 30.0 kg/m^2 and will be acceptable for inclusion.
3. An informed consent document signed and dated by the subject or a legally acceptable representative.
4. Subjects who are willing and able to comply with scheduled visits, treatment plan, laboratory tests, and other study procedures.

##### **4.2. Exclusion Criteria**

Subjects presenting with any of the following will not be included in the study:

1. Evidence or history of clinically significant hematological, renal, endocrine, pulmonary, gastrointestinal, cardiovascular (including hypertension), hepatic, psychiatric (including history of depression or bipolar disorder), neurologic, or allergic (including drug allergies, but excluding untreated, asymptomatic, seasonal allergies at time of dosing) disease or clinical findings at screening.

2. Any condition possibly affecting drug absorption (eg, gastrectomy).
3. A positive urine drug screen.
4. History of regular alcohol consumption exceeding 7 drinks/week for females or 14 drinks/week for men (1 drink = 5 ounces (150 mL) of wine or 12 ounces (360 mL) of beer or 1.5 ounces (45 mL) of hard liquor) within 6 months of screening.
5. History or evidence of habitual use of tobacco- or nicotine-containing products within 3 months of screening or a positive urine or blood cotinine screen.
6. Treatment with an investigational drug within 30 days or 5 half-lives preceding the first dose of study medication.
7. Participation in a previous cohort in this study.
8. Antibiotic treatment within 14 days prior to dosing.
9. Hospitalization for any reason within 90 days prior to dosing, at the discretion of the investigator.
10. 12-lead ECG demonstrating QTc >450 msec at screening. If QTc exceeds 450 msec, the ECG should be repeated two more times and the average of the three QTc values should be used to determine the subject's eligibility.
11. Use of prescription or nonprescription drugs and dietary supplements within 7 days or 5 half-lives (whichever is longer) prior to the first dose of study medication. Herbal supplements and hormone replacement therapy must be discontinued 28 days prior to the first dose of study medication. As an exception, acetaminophen/paracetamol may be used at doses of up to 1 g/day. Nasal decongestants are excluded, except for those solutions containing only saline. Limited use of other non-prescription medications that are not believed to affect subject safety or the overall results of the study may be permitted on a case-by-case basis following approval by the sponsor.
12. Blood donation of approximately 1 pint (500 mL) within 56 days prior to dosing.
13. Consumption of grapefruit or grapefruit-related citrus products within 7 days prior to the first dose of study medication.
14. History of hypersensitivity to or intolerance of linezolid.
15. Diarrhea lasting 7 days or more in the period immediately prior to dosing.
16. Other severe acute or chronic medical or psychiatric condition or laboratory abnormality that may increase the risk associated with study participation or investigational product administration or may interfere with the interpretation of study results and, in the judgment of the investigator, would make the subject inappropriate for entry into this study.
17. Pregnant or nursing females; females of childbearing potential.

18. Unwilling or unable to comply with the Lifestyle guidelines described in this protocol.

#### **4.3. Randomization Criteria**

Subjects will be assigned a unique PIMS number at time of screening. This identifying number will be retained throughout the duration of study participation. Subjects will be randomized into the study provided they have satisfied all subject selection criteria. A computer generated randomization schedule will be used to assign subjects to the treatment sequences.

#### **4.4. Life Style Guidelines**

##### **4.4.1. Meals and Dietary Restrictions**

- Subjects must abstain from all food and drink (except water) at least 4 hours prior to any safety laboratory evaluations and 8 hours prior to the start of pharmacokinetic sample collections (except for Cohort 2, Period 4 described below). Water is permitted until 1 hour prior to study medication administration.
- Water may be consumed without restriction beginning 1 hour after dosing. Non-caffeinated drinks (except grapefruit or grapefruit-related citrus fruit juices – see below) may be consumed with meals and the evening snack.
- Lunch will be provided approximately 4 hours after dosing.
- Dinner will be provided approximately 9 to 10 hours after dosing.
- An evening snack will be permitted up to 2200 hours.
- Subjects will not be allowed to eat or drink grapefruit or grapefruit-related citrus fruits (eg, Seville oranges, pomelos) from 7 days prior to the first dose of study medication until collection of the final pharmacokinetic blood sample of each period.
- Subjects will not be allowed to eat cheese from Day 0 of each period until collection of the final pharmacokinetic blood sample of each period.
- While confined, the total daily nutritional composition should be approximately 50% carbohydrate, 35% fat and 15% protein. The daily caloric intake per subject should not exceed approximately 3200 kcal.
- FED Conditions for Cohort 2, Period 4: Following an overnight fast of at least 10 hours, subjects should start breakfast 25 minutes prior to administration of the drug product. The breakfast will be consumed over a 20-minute period with PNU-100480 administered within 5 minutes after completion of the meal. The drug product should be administered with 240 mL (8 fluid ounces) of water. No food will be allowed for at least 4 hours postdose. Water can be allowed as desired except for

090177e180ac49ac\1.0\Approved\07-May-2009 14:41

one hour before and after drug administration. The breakfast will be a high-calorie/high-fat test meal consisting of two eggs fried in butter, two strips of bacon, two slices of toast with butter, four ounces of hash brown potatoes and eight ounces of whole milk.

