Inhibition of monoamine oxidase (MAO) A and B occurs with LZD, PNU-100480, and its metabolites. Although PNU-100480 is more potent against MAO-A, the major metabolite and major circulating species (PNU-101603) is less potent. In addition, PNU-100480 and the major metabolite are less potent than LZD against the MAO-B target. MAO inhibition may cause hypertension. Such episodes may be precipitated by concomitant use of vasoconstrictors, nasal decongestants, and ingestion of tyramine-rich foods such as cheese. These will be prohibited in the present study, and blood pressure will be closely monitored. MAO inhibition may also precipitate episodes of mania or hypomania in individuals with a history of bipolar illness or depression. Persons with a history of psychiatric illness will be excluded from the present study, and concomitant use of antidepressants will be prohibited.

Isoniazid and rifampin are key components of standard TB therapy. Isoniazid has weak monoamine oxidase inhibitory activity. Adverse events due to concomitant treatment with isoniazid and antidepressants have been reported, although such events appear to be extremely rare. Rifampin is a potent inducer of hepatic CYP3a. CYP3a contributes to metabolism of PNU-100480. Concomitant treatment with rifampin and PNU-100480 may affect relative drug exposures, decreasing that to PNU-100480 and increasing those of its metabolites. MDR and XDR TB are by definition resistant to both isoniazid and rifampin. Neither isoniazid nor rifampin are used in such cases. Specific studies of drug-drug interactions will be required before PNU-100480 is studied with isoniazid and rifampin-containing regimens in patients with drug-sensitive tuberculosis. Isoniazid and rifampin are both excluded as concomitant medications in the present study.

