## 5.5. Concomitant Medication(s)

Subjects will abstain from using prescription or nonprescription drugs, vitamins, and dietary supplements within 7 days or 5 half-lives (whichever is longer) prior to the first dose of study medication and throughout the conduct of the study. Herbal supplements and hormone replacement therapy must be discontinued at least 28 days before the first dose of study medication. Acetaminophen may be used intermittently throughout the study, but should not exceed 1 g/day on two consecutive days, unless greater quantities are deemed necessary by the investigator.

All concomitant medications taken during the study must be recorded with indication, daily dose, and start and stop dates of administration. All subjects will be questioned about concomitant medication at each clinic visit.

Medications taken within 28 days before the first dose of study medication will be documented as a prior medication. Medications taken after the first dose of study medication will be documented as concomitant medications.

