### **6.2.2. Day 1**

**Prior to dosing**, the following activities will be completed:

- Initiate continuous cardiac monitoring at least 2 hours prior to dosing for Period 1 only (see Assessments; Cardiac Monitoring Section). This continuous cardiac monitoring may also be performed anytime after admission, but prior to dosing.
- Assess baseline symptoms/adverse events.
- Obtain triplicate 12-lead ECG measurements (see Section 7.2.3). May insert intravenous catheter for collection of blood samples.
- May insert intravenous catheter for collection of blood samples.
- Assess single supine blood pressure and pulse rate (see Section 7.2.2).
- Collect a blood sample for pharmacokinetic (PK) analysis (see Section 7.3.1).
- Collect whole blood for bactericidal activity (Cohort 1, Period 3 only and Cohort 2, Periods 1, 2 and 3 only, see Section 7.4.1).
- Cohort 2, Period 4 only- subjects should consume high calorie, high fat meal prior to dosing (see Section 4.4.1).
- Administer the study medication as described in the Study Treatments Section and, more specifically, in Administration Section (see Section 5.3.3).

**After dosing**, the following activities will be completed:

- Obtain triplicate 12-lead ECG measurements at approximately 1, 2, 3, 4, 8, and 12 hours after dosing.

090177e180ac49ac\1.0\Approved\07-May-2009 14:41

- Assess single supine blood pressure and pulse rate at approximately 1, 2, 3, 4, 8, and 12 hours after dosing.
- Collect blood samples for pharmacokinetic analysis at 1, 2, 3, 4, 8, 12 and 16 hours after dosing.
- Collect whole blood for bactericidal activity at 2, 3, 6, 12 hours after dosing. (Cohort 1, Period 3 only and Cohort 2, Periods 1, 2, and 3, see Section 7.4.1 for details).
- Maintain continuous cardiac monitoring for 8 hours (or longer if considered clinically necessary by the investigator) following dose administration (see Section 7.2.4).
- Assess symptoms by spontaneous reporting of adverse events and by asking the subjects to respond to a non-leading question such as “How do you feel?” at 1, 2, 4, 8, 12 and 16 hours after dosing.

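### Section 1.2 says tyramine-rich foods will be prohibited, but the diet rule in Section 4.4.1 bars only the example, cheese

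*Protocol*

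**What the plan says.** Protocol Section 1.2 (Background and Rationale) explains that linezolid, PNU-100480 and its metabolites inhibit MAO-A and MAO-B, and that this may raise blood pressure. It then lists what may trigger a hypertensive episode and commits to a precaution: "vasoconstrictors, nasal decongestants, and ingestion of tyramine-rich foods such as cheese. These will be prohibited in the present study". It adds that blood pressure will be closely monitored.

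Protocol Section 4.4.1 (Meals and Dietary Restrictions) holds the diet rules that the unit and the subjects work from. On this subject it has one bullet: "Subjects will not be allowed to eat cheese from Day 0 of each period". The restriction runs until the last pharmacokinetic sample of the period. The only other rule there on the composition of meals during confinement sets approximate proportions of carbohydrate, fat and protein and a calorie ceiling.

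Section 6.1 has subjects instructed on the Life Style Guidelines (Section 4.4) and on concomitant medication. Exclusion criterion 18 in Section 4.2 turns away anyone unwilling or unable to follow the lifestyle rules.

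**The concern.** In Section 1.2 the commitment is to a class of foods, and cheese illustrates it. In Section 4.4.1 the class has gone and only the illustration remains. Section 4.4 is where subjects are told to look and is a condition of eligibility, so it is the text that will shape behaviour and menus. Someone who follows it exactly would comply with the diet rules while still serving or eating other tyramine-rich foods.

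What is at stake is a safety precaution that the protocol sets for itself, in a first-in-human study with planned doses up to 1500 mg. The rule put into operation gives less protection than the rationale promises, and the document gives no reason for narrowing it.

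**Working it through.** No statistical calculation applies. The check sets the commitment beside the sections that could carry it out, then looks at how far the study's other safeguards limit the consequence.

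**1. What Section 1.2 commits to.** The prohibition refers back to the whole list of triggers just named: vasoconstrictors, nasal decongestants and tyramine-rich foods. The words before cheese mark it as an example.

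**2. Where the food item could reappear.** The sections checked were 4.2 (exclusions), 4.4.1 (meals), 4.4.2 (alcohol, caffeine, tobacco), 5.3.3 (administration), 5.5 (concomitant medication), 6.1 to 6.2 (procedures) and the Schedule of Activities. Tyramine is mentioned only in Section 1.2. Section 4.4.1 bars cheese, and none of the others restores the class.

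**3. How neighbouring rules are written.** The bullet directly above the cheese bullet names a food class with examples: "Subjects will not be allowed to eat or drink grapefruit or grapefruit-related citrus fruits (eg, Seville oranges, pomelos". The other MAO precautions reach operating text in differing ways:
- Nasal decongestants are named in Section 4.2, criterion 11: "Nasal decongestants are excluded, except for those solutions containing only saline".
- Psychiatric history is named in criterion 1: "psychiatric (including history of depression or bipolar disorder".
- Vasoconstrictors and antidepressants are not named in Section 4.2 or 5.5. They are caught by the general drug ban: "Subjects will abstain from using prescription or nonprescription drugs, vitamins, and dietary supplements within 7 days or 5 half-lives" and during the study.
- Blood pressure monitoring is scheduled, on Day 1 as follows: "Assess single supine blood pressure and pulse rate at approximately 1, 2, 3, 4, 8, and 12 hours after dosing".

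This comparison suggests a drafting slip and does no more than that. The point rests on steps 1 and 2.

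**4. How long subjects are in the unit.** Admission is on Day 0 and the stay lasts at least 48 hours after dosing (Section 3.1). Where a 72-hour pharmacokinetic sample is taken, discharge moves to Day 4 (Section 6.2.5).
- Dosing periods in all: 3 (Cohort 1) + 4 (Cohort 2) = 7.
- Periods with a 72-hour sample: 2 (Cohort 1, Periods 2 and 3) + 4 (Cohort 2, Periods 1 to 4) = 6.
- The remaining one is Cohort 1, Period 1 (35 mg or placebo), which ends at 48 hours.

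The cheese window closes at the last pharmacokinetic sample. From dosing to the end of the window the subject is therefore in the unit. The hours of Day 0 before admission are the only part of the window spent elsewhere.

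**5. Blood pressure readings after dosing (Sections 6.2.2 to 6.2.5).**
- Day 1: 1, 2, 3, 4, 8 and 12 hours, so 6 readings.
- Day 2: 24 and 36 hours, so 2 readings.
- Day 3: 48 hours, so 1 reading.
- Total to 48 hours: 6 + 2 + 1 = 9. With the 72-hour reading: 9 + 1 = 10.

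Section 4.4.1 puts lunch at about 4 hours and dinner at about 9 to 10 hours. The next reading after lunch time is at 8 hours, or 8 − 4 = 4 hours later. The next after dinner is at 12 hours, or 12 − 10 = 2 to 12 − 9 = 3 hours later.

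**6. Other safeguards.** The unit provides lunch and dinner on the dosing day. The fed-period breakfast in Section 4.4.1 is fixed and contains no cheese. Alcohol is barred from 24 hours before dosing to the last pharmacokinetic sample (Section 4.4.2). Hypertension is an exclusion (Section 4.2, criterion 1). Section 1.2 also notes that the main circulating metabolite is less potent against MAO-A, although the parent is more potent.

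**The case against.** The strongest reply is that Section 1.2 is itself protocol text. Its prohibition is unconditional, and Section 12.2 requires the study to follow the protocol, so the ban on the class already binds the site. On this view Section 4.4.1 merely fails to repeat it. That stands in part. A reader might infer that the two sections contradict each other, but they do not: Section 4.4.1 is silent on other tyramine-rich foods and does not permit them. What remains is that the text subjects are instructed on is narrower than the precaution, and nothing in it sends the reader back to Section 1.2.

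Confinement and unit-provided meals are also a fair reply, and they are why the point is small. For nearly all of the window, exposure would depend on the unit serving such food. But control of the menu helps only if the menu rule tells the unit what to leave out.

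Two stronger readings are tempting, and neither is supported:
- A reader might infer that a food-related pressure rise could halt escalation through the third criterion in Section 3.3: "Clinically significant ECG or BP/HR abnormalities in ≥2 subjects receiving active drug in the same period". That needs clinically significant events in at least two subjects on active drug in the same period. The document offers nothing that links the menu to events of that kind, so this is speculation.
- A reader might infer that food is the one MAO precaution lost while all the others are carried over intact, and express this as a proportion. Vasoconstrictors and antidepressants are covered only by a blanket drug ban, and criterion 11 allows case-by-case approval of some non-prescription medicines. Monitoring is an assessment and not a class of banned items. Any such count would depend on how the items were labelled.

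Finally, the Investigator's Brochure and the consent pages are not available here. Whether other site or subject instructions already cover the class cannot be judged either way.

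**Conclusion.** The point holds as a gap between the stated precaution and the operating rule: Section 1.2 says tyramine-rich foods will be prohibited, and Section 4.4.1 bars cheese alone. It rests on reading cheese in Section 1.2 as an example, which is what the sentence says, and on treating Section 4.4 as the working text for subjects and the unit, which Section 6.1 and exclusion criterion 18 support.

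Its practical weight is small. No pressor risk can be quantified from the document and none is claimed. Confinement to 48 or 72 hours, meals provided by the unit, the alcohol ban, the hypertension exclusion and repeated blood pressure readings all limit the consequence. The dose plan, sample size, endpoints and analysis are unaffected. This is a worthwhile improvement to the wording of a safety rule and not a defect that threatens the study.

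**What to change.** In the Section 4.4.1 bullet, replace *cheese* with *tyramine-rich foods, including cheese*. Keep the existing window, from Day 0 to the last pharmacokinetic sample of each period. Have the clinical research unit check its menu against the reworded rule. The protocol names no tyramine-rich food other than cheese, so the sponsor should supply the list used for that check.

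The cost is one amended bullet, a menu check and a slightly tighter menu. No visit, sample, assessment or analysis changes.
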